### Participants

Patient inclusion and exclusion criteria are listed in Table
1. The sample fulfilling these criteria are considered representative for social phobia patients qualifying for treatment in an outpatient setting. Assuming a drop-out rate of 25% over a period of 2 years, a total of 162 patients are planned to be enrolled in the study (that is 54 patients in each center; see sample size calculation). Patients will only be able to enrol once in the present trial. Participants will be able to directly contact the trial centre in response to advertisements via the internet, flyers, or newspaper articles. Alternatively, they will be referred to by healthcare practitioners (that is, medical doctors or private practitioners in psychotherapy). Once the diagnostician confirms the patient’s eligibility for the study, the patient will select and contact a therapist from a list of candidates for treatment. Only private practitioners officially listed in the German chambers of psychotherapists will be recruited. Informed consent from both the therapist and the patient will be collected. All therapists will have to be certified in CBT. Inclusion criteria for therapists are broad (that is, any age and gender, living in the area of the trial center) as a function of the naturalistic aspects of the present trial. However, practitioners having recent training (within the last 5 years) in the Clark and Wells treatment of SP
[17] will be excluded from the study. Measures of allegiance to the treatment condition and professional experience will be collected via self-report of the therapists as well as via expert ratings of video-documented sessions.

**Table 1 T1:** Inclusion and exclusion criteria

**Inclusion criteria**	Diagnosis of SP (SCID-I)
	Liebowitz Social Anxiety Scale >30 (>60 for generalized subtype)
	Age 18 to 70 years
	SP must be primary diagnosis (most severe disorder according to ADIS-IV)
	SP patients with co-morbid disorders will be included, provided that SP is the primary diagnosis, thus ensuring a clinically representative sample as well as analyses of subgroups (for example, type of SP, patients with co-morbid depressive disorder)
**Exclusion criteria**	Psychotic disorder
	Prominent risk of self-harm
	Acute substance-related disorders
	Personality disorders except for avoidant
	Obsessive-compulsive or dependent personality disorder (SCID-II) organic mental disorder
	Severe medical conditions

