**Figure 2 F2:**
[figure not shown]
**Time points of assessment.** 1) LSAS self rating, 2) LSAS observer rating.

Independent and trained SCID interviewers giving patient assessments are blind to the treatment condition. Assessments will be made at baseline, that is, prior to treatment onset (T1), at session 8 (T2), 15 (T3), and 25 (usually post-treatment, T4), at post-treatment (when treatment duration is longer than 25 sessions, T5). Every session is planned to have a 50-min duration. Follow-up assessments will take place 6 (T6) and 12 months (T7) after treatment; assessments at weeks 8 and 15 are performed to ensure intent-to-treat analyses. Primary endpoint: assessment after 25 sessions; secondary endpoint: post-treatment. Should treatment end at T4, measures for T5 will also be collected.

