### Statistical analysis

#### Primary analyses

The following hypothesis will be tested: H0: μ manualized ≤ μ standard *vs.* H1: μ manualized > μ standardwhere μ manualized and μ standard are the true remission probabilities in the manualized treatment group and the standard routine care group after the treatment period, respectively.

Remission rates will be compared between specifically trained and standard CBT group via logistic regression using covariates for treatment, sex of the therapist, and experience of the practitioner (as in
[37]). For repeated measures, as suggested by 
Wood *et al.*[46], random effects models will be fitted of outcomes taking into account potential drop-outs (for further reference, see
[42] and
[47]). Hypothesis 1 of this trial will be tested by the group*time interaction (with dummy variables coding the time effects at time points T4 to T7 as compared to baseline measurement).

Further analyses will include: comparison of remission rates across treatment groups at time points T4 to T7 using the chi-squared test of independence; cross-sectional analyses at T4 to T7 comparing both patients and therapists in the three study centers; analyses of covariance of outcomes at T4 to T7 considering patient variables, taking into account potential differences between patients recruited by trained *vs.* those recruited by non-trained therapists; and multiple regression analyses to test whether diverse covariates including process variables predict different treatment outcomes. Regression analysis will be applied to each treatment group separately. Should the results be similar, the sample will be pooled.

A descriptive analysis will be made on drop-outs and their covariates. Imputation methods will be considered if necessary following an assessment of the missing value structure
[46].

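### The primary hypothesis is given two unranked, non-equivalent tests, and the second names neither its outcome nor a one-sided contrast

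*Protocol article*

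**What the plan says.** Three places in the protocol article bear on the test of Hypothesis 1.

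- **Statistical analysis, Primary analyses.** The null and alternative are one-sided, and their two parameters "are the true remission probabilities in the manualized treatment group and the standard routine care group after the treatment period, respectively". The method follows: "Remission rates will be compared between specifically trained and standard CBT group via logistic regression using covariates for treatment", together with therapist sex and experience. Random effects models for repeated measures come next, fitted to outcomes that are not named. Then: "Hypothesis 1 of this trial will be tested by the group*time interaction". Time enters that model through four indicators, one for each of T4, T5, T6 and T7, with baseline as the reference. Nothing ranks the logistic regression against the interaction.
- **Assessment.** "Primary endpoint: assessment after 25 sessions; secondary endpoint: post-treatment". This makes T4 the primary time point, T5 secondary, and T6 and T7 the 6- and 12-month follow-ups.
- **Sample size calculation.** The stated aim is a sample size for a dichotomous approach based on remission. In the primary ITT analysis, drop-outs count as not remitted. Alpha is 0.05, one-tailed, and the Discussion defends that choice.

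Two definitions also matter. Entry requires "Liebowitz Social Anxiety Scale >30 (>60 for generalized subtype" (Table 1), and Outcomes defines remission as an LSAS total of 30 or less.

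**The concern.** A confirmatory trial needs one test that decides its primary hypothesis. Here two analyses under one heading can each claim that role, and they can disagree. One asks whether more patients of trained therapists are in remission. The other asks whether the groups differ in change from baseline over four later occasions, on an outcome left open. If the choice is made after the results are known, the 5% error rate no longer describes the procedure.

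The article commits itself to both tests, so this is a stated conflict and not detail left to a statistical analysis plan. Random effects analyses of the other scales appear separately under Secondary analyses, so the heading does not demote the interaction either.

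**Working it through.** **1. The two tests side by side**

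| Feature | Logistic regression | Group-by-time interaction |
|---|---|---|
| Outcome | Remission (LSAS 30 or less) | Not named |
| Time | After the treatment period | T4, T5, T6 and T7, each against baseline |
| Treatment terms | 1 | 4 |
| One-sided direction | Stated in H0/H1 | No contrast named |
| Drop-outs counted as not remitted | Fits | Fits only if the outcome is remission |

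**2. If the interaction is on continuous LSAS.** It can be estimated. But it compares mean change, while the stated H0 compares remission probabilities. The drop-out rule cannot be applied to it, and the sample size section says it is aimed at the dichotomous outcome.

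**3. If the interaction is on remission.** Let p(g,t) be the remission probability in group g at time t. The T4 interaction is

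[logit p(1,T4) − logit p(1,T1)] − [logit p(0,T4) − logit p(0,T1)].

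With entry above 30 and remission at 30 or below on the same LSAS version, p(1,T1) = p(0,T1) = 0. Both baseline logits are minus infinity and their difference is undefined.

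An illustration used simulated data: 58 per group, no baseline remissions, and assumed remission probabilities of 0.45 and 0.25 at each later occasion. It was an ordinary logistic fit without random effects.

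| Iterations | Intercept | SE of group-by-T4 |
|---|---|---|
| 10 | −11.2 | 30.5 |
| 20 | −21.2 | 4,527 |
| 25 | −26.2 | 55,147 |

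Only the sum of the group and group-by-T4 terms is stable. At 0.757 it equals the plain T4 log odds ratio in the same data, so the identifiable part is the cross-sectional comparison at T4. A random intercept does not help, because every baseline outcome is still zero.

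**4. If the four coefficients are tested jointly.** The usual joint test is chi-squared with 4 df and a 5% critical value of 9.488. Assume correlation 0.7 between the four statistics and equal effects at T4 to T7, sized so that the one-sided T4 test has 80% power. The shift is then 1.645 + 0.842 = 2.486 before rounding, and the noncentrality is 4 × 2.486² / (1 + 3 × 0.7) = 7.98. The joint test rejects in about 60% of trials when the effect is benefit and in about 60% when it is equal harm. The one-sided T4 test rejects in 80% and in fewer than 0.01%. An ordinary joint test therefore cannot serve a one-sided hypothesis.

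**5. Error rate.** The plan's own figure is 5% for one one-sided test. For k tests, each at z > 1.645, with common correlation ρ, the chance of at least one false success is 1 − P(all k statistics ≤ 1.645). The correlations are assumptions; the documents give none.

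| ρ | 2 tests | 4 tests |
|---|---|---|
| 0.5 | 8.8% | 14.4% |
| 0.6 | 8.4% | 13.3% |
| 0.7 | 8.0% | 12.0% |
| 0.8 | 7.5% | 10.6% |

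The two-test column covers the case where success on either the logistic test or the T4 interaction contrast would count. The four-test column covers the case where success at any of T4 to T7 would count.

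**The case against.** The strongest reply is that the document mostly points one way. H0, the stated aim of the sample size, the drop-out rule and the primary time point all fit remission at T4 by logistic regression. The random effects models are introduced for repeated measures, after remission has been given its own method, and the LSAS is the primary outcome measure. The natural reading is therefore a mixed model on LSAS scores, which can be fitted. A statistical analysis plan, not shown here, could name the contrast.

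Much of this stands, and it rules out several stronger conclusions that a reader might draw:

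- **The primary model will fail to fit.** This follows only if the outcome is remission and the same LSAS version is used at entry and outcome. Figure 2 lists self and observer ratings, and the text does not settle which applies.
- **No one-sided test exists for four coefficients.** Such tests exist, and a one-sided T4 contrast comes straight from the model. The fault is that none is named.
- **The error rate is 10.6% to 14.4%.** Nothing says that success at any of T4 to T7 counts, and Assessment singles out T4. If T4 and T5 coincided for most patients, the count would be nearer three tests (11.8% at 0.5, 9.3% at 0.8).
- **One measurement enters the model twice.** The text says only "Should treatment end at T4, measures for T5 will also be collected". That one record is copied into two occasions is an inference.

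The reply does not remove the sentence that assigns Hypothesis 1 to the interaction. Reading that model as continuous LSAS avoids the fitting problem but confirms that it tests something other than the stated H0.

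**Conclusion.** The point holds as a contradiction within Primary analyses: Hypothesis 1 has two unranked tests that do not address the same quantity, and the second goes beyond the single primary time point. On either reading of its outcome, the interaction cannot stand in for the stated one-sided test on remission. It addresses a different parameter if continuous, and has no finite estimate if it is remission measured with the entry version of the LSAS.

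The exposure is a one-sided error of about 7.5% to 8.8% in place of 5%. This assumes that success on either the logistic test or the T4 interaction contrast would be accepted, with correlation between 0.8 and 0.5. The higher four-test range needs a success rule that the document does not contain. The contradiction itself rests on the text alone and needs none of these assumptions.

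**What to change.** 1. State that Hypothesis 1 is tested only by the one-sided 5% test of the treatment coefficient in the logistic model for remission at T4. Name T4 in H0 as well, because that text now refers only to the end of the treatment period.
2. Delete the sentence that assigns Hypothesis 1 to the interaction, or relabel it so that the repeated-measures model is secondary.
3. State that this secondary model is fitted to continuous LSAS, and that its single named contrast is the group difference in change from baseline at T4. Describe the estimates at later time points as supportive.

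This follows the protocol's own hypothesis, primary time point, drop-out rule and stated sample size aim. It costs a wording amendment and needs no new data or visits. It should be made before outcomes are seen by group, since a choice made afterwards cannot restore control of the error rate.

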### Randomization

Therapists will be randomly assigned either to a training group (manualized CBT), in which they will undergo an intensive training of the treatment manual for social phobia, or to a control group (routine care), in which the non-manualized CBT standard treatment is applied. Private practitioners will be block randomized. Practitioner randomization will be stratified for each trial center using the nQuerie Advisor® 6.01 software program
[44]. As participants in a naturalistic study, patients are not randomized and have no knowledge on whether or not the therapist they have freely chosen has been trained in manualized CBT. Diagnostic procedures are performed by independent, blinded, and specially trained assessors for diagnosis and observer-rated outcome measures. All diagnosticians are trained by one of the co-authors (US), who was responsible for quality assurance of CBT in the SOPHO-NET study and has extensive experience in conducting RCT of SP
[43,45]. There will be multimethod assessment of specific and non-specific therapy outcome including both patient and assessor perspective; control for drop-outs, intent-to-treat analyses. Generalizability of results will be established by above defined inclusion and exclusion criteria (Table
1) and by the multicenter approach.

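### Trial therapists who know their arm are not excluded as referrers, so entry is not concealed for any patient whom a trial therapist both refers and treats

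*Protocol article*

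**What the plan says.** The unit of randomisation is the therapist (Protocol article, Randomization): "Therapists will be randomly assigned either to a training group (manualized CBT), in which they will undergo an intensive training of the treatment manual". Patients are not allocated by the trial. The same section says that "patients are not randomized and have no knowledge on whether or not the therapist they have freely chosen has been trained in manualized CBT". Diagnosis and observer-rated outcomes are in the hands of independent, blinded assessors.

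Participants gives two ways in. The first is self-referral: "Participants will be able to directly contact the trial centre in response to advertisements via the internet, flyers, or newspaper articles". As the alternative, "they will be referred to by healthcare practitioners (that is, medical doctors or private practitioners in psychotherapy"). The order after that is stated: "Once the diagnostician confirms the patient’s eligibility for the study, the patient will select and contact a therapist from a list of candidates for treatment".

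The Primary analyses section, in its list of further analyses, foresees analyses of covariance on patient variables at T4 to T7, "taking into account potential differences between patients recruited by trained" therapists and those recruited by non-trained ones. The logistic model for remission lists treatment, therapist sex and therapist experience. It lists no patient baseline variable.

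**The concern.** When clusters are randomised and patients enter afterwards, randomisation protects the comparison only if entry into each cluster does not depend on the cluster's arm. Here the cluster is a therapist who has or has not attended two training blocks and cannot be blind to that. If such a therapist can put patients forward and then treat them, he or she chooses them with the arm known. A trained therapist might favour patients who seem suited to the manual; an untrained one might refer fewer or different patients.

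The masking described in the article covers the patient, the eligibility decision and the outcome rating. It does not cover who is put forward. At stake is the remission comparison, tested one-sided in favour of training. Selection that favours the trained arm raises the false-positive rate; selection the other way can hide a real benefit.

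**Working it through.** **Step 1. The passages side by side.**

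| Question | Participants / Randomization | Primary analyses |
|---|---|---|
| Who brings the patient in? | The patient, a doctor, or a private psychotherapist | A trained or a non-trained therapist |
| Who fixes the arm? | The patient, by choosing from the list after eligibility is confirmed | Not stated; the wording ties recruitment to the therapist |
| Who knows the arm at that point? | Not the patient, not the diagnostician | The therapist |

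Trial therapists are private practitioners in psychotherapy, so the referral clause includes them unless another rule takes them out, and the article states none. It also states no rule against choosing the referring therapist from the list.

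**Step 2. Which patients are exposed.** A patient who answers an advertisement has no therapist-recruiter. A patient referred by a doctor or by a therapist outside the trial is put forward by someone with no arm. A patient referred by a trial therapist who then picks another therapist does not enter the referrer's cluster. That leaves patients whom a trial therapist both refers and treats. Their share is not given.

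**Step 3. What the planned adjustment reaches.** The analysis of covariance on patient variables is a further analysis and is not part of the logistic remission model. The group-by-time test of hypothesis 1 takes account of baseline level on the outcome. Neither removes differences in motivation or expected response that are not measured.

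**Step 4. Illustration of size.** Inputs from Sample size calculation: one-sided α = 0.05 (z = 1.645), d = 0.50, m = 5, ICC = 0.15, 58 per group. Assumed, not in the documents: a net shift b in prognosis between arms.

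- Design effect: 1 + (5 − 1) × 0.15 = 1.6.
- The plan's own figure: 2 × [(1.645 + 0.842)/0.50]² × 1.6 = 49.46 × 1.6 = 79.1, or 80 per group. The stated 58 does not reproduce. That is a separate matter; 58 is used here because it is the stated target.
- Standard error in SD units: √(2 × 1.6/58) = 0.235.
- Rejection rate when training has no effect: Φ(b/0.235 − 1.645).
- Power at a true d = 0.50 when the shift runs against training: Φ((0.50 − b)/0.235 − 1.645).

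| Net shift b (SD) | One example of its origin: share × difference | False-positive rate, shift favours training | Power, shift against training |
|---|---|---|---|
| 0 | none | 5.0% | 69% |
| 0.05 | 0.25 × 0.2 | 7.6% | 61% |
| 0.10 | 0.50 × 0.2 | 11.1% | 52% |
| 0.15 | 0.50 × 0.3 | 15.7% | 44% |

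A shift of 0.05 to 0.15 SD is 10% to 30% of the planned d = 0.50. If all 162/2 = 81 enrolled patients per arm are analysed, with drop-outs counted as not remitted, the standard error is √(2 × 1.6/81) = 0.199 and the three false-positive rates become 8.2%, 12.7% and 18.7%. The calculation is on the standardised scale that the plan uses for its sample size, not on remission itself.

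**The case against.** The strongest reply is that the stated order of events already protects entry. A blinded, independent diagnostician decides eligibility first, and only then "the patient will select and contact a therapist from a list of candidates for treatment". On that reading a referrer cannot know where the patient will go, and the recruitment phrase under Primary analyses is loose wording for patients treated by each group. The referrers named are a general class and are not identified with the 36 trial therapists. Handling of the list and of referrals may stand in the full protocol, which is not shown. The order of training and recruitment is also only inferred, from the statement that patients do not know whether the chosen therapist has been trained; the trial-flow figure is not available. Finally, the article foresees patient differences and plans an adjustment.

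Much of this stands, and it limits the point. A reader might infer that the recruiter knows every patient's arm and that allocation is unconcealed throughout the trial. The documents do not support that: advertisement patients have no therapist-recruiter, and the list choice comes after a blinded eligibility check. They also do not show that any trial therapist referred a patient, or that bias occurred.

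Two things remain. The article makes two statements about how patients reach therapists that do not fit each other, on a step that validity depends on. And the plan as written permits self-referral by therapists who know their arm, while the adjustment it foresees lies outside the remission model and cannot reach unmeasured selection.

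**Conclusion.** The point holds in a limited form. For patients whom a trial therapist refers and then treats, entry is not concealed from the arm, and selective referral could bias the remission comparison in either direction. For other patients this route does not exist. Whether the exposed share is negligible or large cannot be told from the article.

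The size is illustrative only: a net shift of 0.05 to 0.15 SD takes the one-sided 5% error to about 8% to 16% at 58 per group and a design effect of 1.6. The arithmetic is sound, but the shift has no source in the documents and should not be read as an estimate of actual bias. The conclusion also assumes that training precedes at least part of recruitment. It calls for a cheap improvement and does not invalidate the design.

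**What to change.** 1. Reconcile Primary analyses with Participants: say whether trial therapists may refer patients, and whether the covariance analysis concerns patients recruited by or treated by each group.
2. Send every patient, including one referred by a trial therapist, through the centre's eligibility check and therapist list. Show the list in random order and keep the patient's free choice.
3. Record the referral source at enrolment: trial therapist and arm, or other.
4. Pre-specify a sensitivity analysis of the primary remission endpoint that excludes patients treated by the therapist who referred them, and report how many are excluded in each arm.

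Forcing equal numbers from each arm onto the list is not needed and would alter the naturalistic choice process during recruitment.

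Cost: one enrolment field, a shuffled list and one extra analysis. Therapist-referred patients have slightly less direct access to their referrer, and the sensitivity analysis has fewer patients and so less precision. Trial status says that recruitment is ongoing. The referral field and the sensitivity analysis can still be added; a change to the list should be dated, so that patients entered before and after it can be told apart.
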